### 2.8. Outcomes and measurements

#### 2.8.1. Participant characteristics.

Characteristics of participants will be collected through a self-report online survey developed by the research team (S2 File), which was also used in earlier stages of the IHC-C programme (31). The survey will gather the following information:

Demographic data: age, gender, educational background, ethnic background, employment status, and internet accessibility.Cancer-related information: how the participant is impacted by cancer (as outlined in the ‘Eligibility criteria’ section), cancer diagnosis, time since diagnosis (for patients and survivors), and the relationship between current patients/survivors and their informal carers/loved ones.

#### 2.8.2. Primary outcomes.

The primary outcomes will assess feasibility and acceptability. Outcomes will be gathered through a structured survey, designed using standard recommendations for pilot RCTs and instruments from similar intervention studies, and tailored to this trial’s specific needs (S2 File).

Feasibility

Recruitment efficiency: the number and proportion of participants who were approached, consented, deemed eligible, and randomised within the recruitment period. Data will be monitored using trial recruitment logs.Retention: the number and proportion of participants who remain in the programme from baseline to the final outcome assessment. Data will be collected from the online learning platform.Adherence: the extent to which participants follow the intervention protocol and engage with the programme, which includes login frequency, time spent on the platform, and interaction with programme materials. Data will be collected through the online learning platform, noting any missed or incomplete units and documenting the reasons for non-adherence via system-generated inactivity logs of the learning platform.Technical feasibility: the capability of the online platform to deliver the intervention and support user access. Data will be gathered through a participant survey evaluating ease of access and any technical problems encountered (S2 File). In addition, technical support logs will also record system issues and user-reported difficulties. We do not intend to extract backend data directly from Moodle for this pilot study.Data collection efficacy: the number and proportion of completed outcome assessments and identification of any issues with measurement tools. Data will be collected through the online learning platform.

Acceptability

Participation rates: the number and proportion of participants who complete individual units and assigned activities. Data will be collected through the online learning platform.Participation burden: assessment of the effort required by participants to engage with the programme and complete tasks. Data will be gathered through participant survey questions regarding perceived efforts and whether participants found it acceptable. This will include both the burden of engaging with the intervention and completing outcome assessments.Participants’ perspectives: based on participant response to open-ended questions about participants’ experience with each unit and the overall programme. Data will be collected through survey questions.General acceptability: participants’ perceptions of the programme, including their views on its content, format, duration, overall acceptability, and willingness to recommend. Data will be collected through survey questions.

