**Discussion:**

This pilot trial will inform the design and conduct of a future definitive randomised trial. Insights gained will inform sample size estimations, refine recruitment strategies, optimise programme delivery, and improve data collection processes, ensuring a robust and scalable approach for the definitive trial.

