#### 2.7.2. Intervention group.

Participants randomised to the intervention group will be given access to the IHC-C programme after allocation. The intervention will occur over four weeks. Participants will be encouraged to follow the intervention instructions and complete the programme at their own pace within the four weeks. Those who have not started or completed the programme will receive a follow-up email reminder at the beginning of the final week. Additional support will be offered to participants who show low engagement early in the intervention period, including automated reminders and, where appropriate, personalised follow-up emails to encourage ongoing participation. Email support will be available to all participants, with responses typically provided within 24 hours. A certificate of completion will be awarded to those who finish the programme.

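### The platform inactivity logs named as the source for reasons for non-adherence can show what was missed and when, but not why

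*Protocol article*

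**What the plan says.** Section 2.8.2 makes adherence one of the primary feasibility outcomes and measures it by "login frequency, time spent on the platform, and interaction with programme materials". Missed or incomplete units are to be noted, and the same sentence goes on to "documenting the reasons for non-adherence via system-generated inactivity logs of the learning platform". No other source is attached to the reasons.

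The next item in that section, technical feasibility, ends with the statement "We do not intend to extract backend data directly from Moodle for this pilot study".

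Section 2.7.2 provides for contact with people who fall behind: "Those who have not started or completed the programme will receive a follow-up email reminder at the beginning of the final week". It adds personalised emails where early engagement is low. The stated purpose of those emails is encouragement, not data collection.

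The Discussion paragraph of the abstract sets out what the pilot is for: "Insights gained will inform sample size estimations, refine recruitment strategies, optimise programme delivery, and improve data collection processes".

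**The concern.** A reason is something only the participant, or someone who has asked the participant, can report. A log generated from inactivity records the absence of events: who, which unit, from what date. Two participants who stop at the same unit on the same day leave the same trace, even if one was unwell and the other found the material too long. The protocol has not left the source open for a fuller document to settle. It has named one, and that source cannot hold the variable.

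The pilot is meant to guide changes in programme delivery before a definitive trial, and different causes of non-adherence call for different changes. If the marks in section 2.9.2 for adherence (50% of participants) or per-unit participation (above 70%) are missed, the counts will show that the programme fell short. The team will then want to know why, and the data assigned to that question will not say.

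**Working it through.** The plan states no figure for this item, so the check is a reading of every data source that could carry reasons, followed by simple arithmetic for scale.

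**Sources set side by side (protocol article)**

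| Source | Section | Purpose stated | Described as asking why? |
|---|---|---|---|
| Inactivity logs | 2.8.2, adherence | Reasons for non-adherence | Assigned to it, but cannot record it |
| "participant survey evaluating ease of access and any technical problems encountered" | 2.8.2, technical feasibility | Access and technical faults | No; could reveal technical causes |
| "technical support logs will also record system issues and user-reported difficulties" | 2.8.2, technical feasibility | Platform faults | No; could reveal technical causes that are logged or reported |
| "participant survey questions regarding perceived efforts and whether participants found it acceptable" | 2.8.2, participation burden | Effort | No; could reveal burden |
| Views on content, format and duration | 2.8.2, general acceptability | Satisfaction | No; could reveal length or content problems |
| Open-ended questions | 2.8.2, participants' perspectives | Experience of units and programme | No; reasons may be volunteered |
| Support when the quiz causes difficulty | 2.7.1 | Help or another way to give feedback | No; limited to the quiz |
| Reminder and follow-up emails | 2.7.2 | Encouragement | No collection of reasons stated |

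Two general statements also bear on this. Section 2.8.2 opens by saying that the primary outcomes are gathered through a structured survey (S2 File), and section 2.9.2 analyses feasibility outcomes with survey responses alongside counts. Survey data on adherence are therefore not ruled out. The article does not describe any item on reasons, and S2 is not shown.

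**Scale**

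- Recommended time, from nine units of 40–45 minutes (section 2.7.1): 9 × 40 = 360 to 9 × 45 = 405 minutes.
- Adherence threshold of 75% of that time (section 2.9.2): 0.75 × 360 = 270 to 0.75 × 405 ≈ 304 minutes.
- Participants who could fall below the threshold with the 50% mark still met: 0.50 × 30 = 15 if the denominator is the 30 in the intervention group, or 0.50 × 60 = 30 if all randomised participants count, since the waitlist group also takes the programme later (section 2.7.3). Section 2.9.2 says only participants, so the denominator is an assumption here.

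The 15–25% in section 2.4 is anticipated attrition. It is not a non-adherence rate and is not used here.

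**Access to the logs**

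The statement "We do not intend to extract backend data directly from Moodle for this pilot study" sits under technical feasibility and may apply only there. It also says directly, which leaves room for standard platform reports. Even so, it sits awkwardly beside an adherence outcome built on logins, time, interaction and system-generated logs. The main point does not depend on it: full access to the logs would still give no reasons.

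**The case against.** A reader might infer that the pilot will end with no information on why people stopped, or that a primary outcome cannot be obtained. The document does not support either reading.

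- The survey introduced at the head of section 2.8.2 covers the primary outcomes in general, and S2 may already contain a question on non-completion. Its absence is not shown.
- Several plausible causes overlap with data that will be collected: technical faults, perceived effort, duration and content, and unit-level experience in free text.
- The outcome is adherence, which is defined by platform use and judged on time alone. Reasons are an accompanying item, and no success criterion uses them.
- Anyone who has disengaged may not answer a new question either, so the remedy shares a limit with the existing survey.

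All four stand, and they confine the point to the route the protocol names. They do not remove it. If S2 asks for reasons, the sentence cites the wrong source. If it does not, reasons will be known only where someone happens to volunteer them under another heading. The sentence needs changing in both cases.

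**Conclusion.** The point holds for the named route. Inactivity logs can detect and date non-adherence but cannot explain it, and no other source in the article is described as asking for the explanation.

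The consequence is moderate. No estimate, sample size or pass mark changes. What is weakened is the pilot's ability to say what to alter if the adherence or per-unit participation mark is missed. The number of people concerned could reach 15 of 30, or 30 of 60 under the wider denominator, without the adherence mark failing, and more if it fails.

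The conclusion rests on reading an inactivity log in its ordinary sense, as an automatic record of non-use with no prompt to the participant. It makes no assumption about what S2 contains. The change is worth making because the contacts needed for it are already planned.

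**What to change.** 1. Reword the adherence item in section 2.8.2 so that platform logs serve only to identify which units were missed and when activity stopped.
2. Name the participant as the source of reasons. Add one short optional item, a tick list with free text (for example illness or treatment, time, length, difficulty, technical problem, not relevant, other), to the final-week reminder email, the T1 survey and any withdrawal contact. If S2 already has such an item, cite it instead.
3. For the waitlist group, T1 falls before programme access and section 2.8.4 lists no later assessment. The reminder email, which section 2.7.3 extends to that group, is therefore the natural place for the item if their reasons are wanted.
4. Report reasons with the number asked and the number responding.
5. State whether the sentence on Moodle backend data is limited to technical feasibility, and how login, time and inactivity records will be obtained.

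The cost is one survey item, one link in emails already planned, and a few words of text. The limitation is incomplete response among those who disengage, which item 4 makes visible.

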#### 2.8.3. Secondary outcomes.

This pilot trial will also collect outcomes intended for the future definitive trial, focusing on:

Critical thinking and decision-making skills involve participants’ ability to appraise evidence, identify misleading claims, and assess the reliability of health information, enabling them to make well-informed decisions learned from the intervention. Data will be collected post-intervention using the structured evaluation tool *Critical Thinking in Cancer and Health Information Evaluation: Scenario-Based Assessment, which includes* four scenarios with 17 questions developed specifically for the IHC-C programme.eHealth literacy: participant’s experience using the internet for health information, measured with the 8-item eHealth Literacy Scale (eHEALS) [47] post-intervention.Cognition and behaviour change: participants’ self-reported changes in understanding and approach to engaging with information. Data will be collected through two specific questions.

#### 2.8.4. Assessment timeline.

Assessments will occur at four time points (see Fig 1):

T − 1 (Baseline assessment): All participants will complete baseline assessments.T0 (Allocation): Randomisation and assignment to the intervention or waitlist control group. No assessments are conducted at this timepoint.T1 (Post-intervention: 4 weeks): Both groups complete assessments – intervention group after completing the programme, control group without programme access.T2 (Control access: 6 weeks): Waitlist control group receives programme access.

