#### 2.7.3. Waitlist control group.

Participants assigned to the waitlist control group will gain access to the IHC-C programme after four weeks, once the intervention group completes the programme and assessments. Participants in the waitlist group will then have four weeks to complete the programme, during which they will receive the same support, reminders, and resources as those in the intervention group. All data collection, including baseline and follow-up assessments, will be conducted using the same tools and methods to ensure comparability of outcomes across both groups. As the primary aim of this pilot study is to inform the design of a future definitive trial, this waitlist control design allows for a controlled comparison of feasibility and acceptability between groups during the intervention phase, while ensuring that all participants ultimately receive access to the programme.

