### 2.9. Statistical analysis plan

Data will be analysed following the intention-to-treat principle. Missing data will be addressed using multiple imputation techniques [48]. Data will be stored and processed using Microsoft Excel, SPSS 28.0, and NVivo 20 Pro. No serious negative outcomes are anticipated for participants; therefore, an interim analysis will not be conducted and no formal stopping rules have been established.

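### The T1 wording describes intervention participants as assessed after finishing the programme and does not say that non-completers are assessed, which is in tension with intention to treat

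*Protocol article*

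**What the plan says.** All places are in the protocol article.

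- **Section 2.8.4 (Assessment timeline)** opens the T1 entry with one time point for both arms: "T1 (Post-intervention: 4 weeks): Both groups complete assessments". It then describes the arms separately: "intervention group after completing the programme, control group without programme access".
- **Section 2.7.2 (Intervention group)** makes the programme self-paced. Participants are encouraged to "complete the programme at their own pace within the four weeks". It also foresees that some will not: "Those who have not started or completed the programme will receive a follow-up email reminder at the beginning of the final week".
- **Section 2.7.3 (Waitlist control group)** opens control access "after four weeks, once the intervention group completes the programme and assessments".
- **Section 2.9** states the analysis principle, "Data will be analysed following the intention-to-treat principle", and adds "Missing data will be addressed using multiple imputation techniques".
- **Section 2.9.3** compares mean changes between the arms at the end of the intervention for critical thinking, decision-making skills and eHealth literacy.
- **Section 2.9.2** counts data collection as successful if 90% of all required assessments are completed. It does not define which assessments are required.

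No section says that a non-completer is assessed at week 4, and none says that a non-completer is not.

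**The concern.** T1 in the intervention arm is described by an event that happens after randomisation and can happen in that arm only. Someone who stops halfway never reaches that event. Staff sending the T1 survey could follow either the four-week label or the completion clause, and the two give different sets of respondents.

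Under the completion clause, three things are at stake:

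1. **Secondary outcomes.** Completers would be compared with controls who passed through no such filter. If completers tend to score higher anyway, the difference favours the programme, and the figures carried into the definitive trial inherit that.
2. **The 90% data-collection criterion.** This is a primary feasibility outcome, and its denominator depends on whether a non-completer's T1 is due.
3. **Burden and general acceptability (75% criteria).** If these questions are asked at T1, people who found the programme too long or too hard would be missing from the answers.

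**Working it through.** **Which reading does the text fix?** The four-week label and the four-week programme window support a calendar reading. The completion clause in 2.8.4 and the similar condition in 2.7.3 support a completion reading. The two agree only if everyone finishes, and 2.7.2 expects that some will not. The article therefore does not settle the case of the non-completer.

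**Plan figures.** The article gives no completion rate, so there is no stated figure to reproduce on this point. The nearest is the attrition of 15% to 25% in section 2.4: 30 × 0.85 = 25.5 and 30 × 0.75 = 22.5, against the stated 20–25 per group. The change proposed here leaves the 30 per group as it is.

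**Possible shift if only completers are assessed (illustration).** Let a share c complete, chosen by a standard normal propensity that has correlation r with the T1 score. Assume no programme effect and no selection in the control arm. The completers' mean is shifted by r × φ(z)/c, where z is the cut-off that leaves the share c above it.

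| c (assumed) | φ(z)/c | r = 0.2 | r = 0.4 |
|---|---|---|---|
| 70% | 0.497 | 0.10 SD | 0.20 SD |
| 50% | 0.798 | 0.16 SD | 0.32 SD |

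A second model uses an assumed completer versus non-completer difference D, giving a shift of (1 − c) × D. For D = 0.2 to 0.8 SD:

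- c = 50%: 0.10 to 0.40 SD
- c = 70%: 0.06 to 0.24 SD
- c = 75%: 0.05 to 0.20 SD
- c = 85%: 0.03 to 0.12 SD
- c = 100%: zero

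The 75% and 85% rows apply if the attrition range is read as non-completion. None of c, r or D is in the article. The 50% and 70% values are borrowed from the adherence and retention criteria, which are not completion rates.

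**Does imputation remove it?** If T1 is collected only after completion, every observed intervention score belongs to a completer. Standard multiple imputation within that arm would give non-completers completer-like values, and no observed non-completer is available to correct them. Baseline scores would help in part, but section 2.8.3 describes both the critical-thinking tool and eHEALS as collected post-intervention. Section 2.9.3 nevertheless speaks of mean changes, so it is uncertain whether baseline scores exist.

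**The 90% criterion.** Take 30 per arm, one baseline and one T1 assessment each, and nothing missing except T1 from intervention non-completers.

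- 15 non-completers: 60 + 45 = 105 assessments completed. If their T1 is not due, 105/105 = 100% (pass). If it is due, 105/120 = 87.5% (fail).
- 9 non-completers: 60 + 51 = 111 completed. If their T1 is due, 111/120 = 92.5% (pass).
- Turning point: 0.90 × 120 = 108, so the result changes with the definition only when more than 12 of the 30 are not assessed.

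**The case against.** The strongest reply is that T1 has a calendar anchor. One label, four weeks, covers both groups. The control half of the clause describes an exposure state, so the intervention half can be read the same way: the state of that arm when its four-week window closes. In section 2.7.3 the words on completion likewise follow a four-week date. No completion-triggered survey is described. The schedule figure is not shown, and an article may leave the invitation procedure to the full protocol.

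Much of this stands. A reader might infer that the plan compares completers with all controls, or that it flatly contradicts intention to treat. The documents support neither: no analysis set is limited to completers, and section 2.9 states intention to treat with imputation. Nor does the adherence criterion forecast heavy non-completion. It is a minimum success threshold, and it concerns time on the platform. A reader might also think that the completion reading creates unequal delays between learning and testing. In fact it puts that delay near zero for every completer; a fixed week-4 survey is what makes it vary. Finally, the comparison concerns secondary outcomes in a 60-person pilot, and no efficacy decision rests on it.

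What does not fall away is that completion appears in two sections, non-completers are expected, and their T1 is not addressed. The benign reading has to be supplied by the reader.

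**Conclusion.** The point holds as an ambiguity with a real consequence if the clause is followed literally. It is not an outright contradiction or a demonstrated bias. On the literal reading, intervention-arm T1 data come only from completers, which defeats the purpose of the stated intention-to-treat principle and cannot be recovered by imputing from completers.

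The likely direction favours the programme, provided completers would score higher regardless of it. The size is unknown. About 0.1 to 0.3 SD follows from assumed completion of 50% to 70% and correlations of 0.2 to 0.4; the second model spans 0.06 to 0.40 SD at the same completion rates. If everyone randomised is assessed at week 4, this source of shift disappears.

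The 90% criterion can change from pass to fail with the definition of a required assessment, but only with more than 12 of 30 intervention participants unassessed and no other losses. The effect on the burden and acceptability answers depends on those questions being asked at T1. This is a cheap improvement worth making, because outcomes that were never requested cannot be restored in the analysis.

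**What to change.** 1. In section 2.8.4, replace the completion clause with a statement that T1 is sent to every randomised participant in both arms four weeks after randomisation, within one common window, whether or not the programme was started or finished.
2. In section 2.9.2, state that all of these count as required assessments for the 90% criterion.
3. Reword section 2.7.3 so that it does not depend on the intervention group completing the programme.

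The common window has to close before controls gain access. Section 2.7.3 places that access after four weeks and section 2.8.4 at six weeks. That is a separate discrepancy, but the two passages must be reconciled before the window is set.

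The cost is a few sentences and a date-based survey invitation, with no change to sample size, staff or instruments. There are two downsides. The effect, completeness and acceptability figures may look slightly less favourable. And early finishers will be tested some time after their last unit: nine units of 40–45 minutes make 360–405 minutes, or 6.0–6.75 hours, so finishing well before week 4 is possible.
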